The clinical management of eoPE remains complex, as clinicians must balance the maternal risks of disease progression against the potential neonatal benefits of pregnancy prolongation. In the absence of complications, most international guidelines recommend delivery at 34 weeks’ gestation to optimize neonatal outcomes [11]. However, prolonging pregnancy to reach this threshold carries significant maternal risks [12]. Observational data indicate that approximately one in three women managed expectantly experiences a major maternal complication requiring intensive care, including HELLP syndrome (12%), placental abruption (11%), pulmonary edema (3%), or renal failure (4%) [13]. The strategy of continuing pregnancy until 34 weeks is based primarily on two clinical trials conducted in the 1990s [14, 15], and a subsequent systematic review incorporating more recent studies concluded that further evidence is needed to establish its safety for the mother [12]. Even under optimal conditions and with careful case selection, the median duration of pregnancy prolongation achieved through expectant management is around seven days (standard deviation: 2–18 days) [14]. While this short gain may be crucial for neonatal outcomes in extremely preterm stages, its benefit becomes less justifiable beyond 30 weeks, when neonatal survival rates in tertiary centers reach 97% at 30–32 weeks (90% without severe morbidity) and 99% at 32–34 weeks (98% without severe morbidity) [16–18].

Another clinical difficulty lies in the administration of corticosteroids for fetal lung maturation. A complete course administered within the week prior to birth significantly reduces neonatal morbidity and mortality, with an adjusted odds ratio of 1.46 (95% CI: 1.20–1.77) compared to administration more than a week before delivery [19]. However, repeated courses appear to be counterproductive, particularly in the long term [20]. Current recommendations therefore favor a single course administered within seven days of delivery [21], a goal that is difficult to achieve in eoPE because of the unpredictable rate of disease progression [22].

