### Objectives

The primary objective of this study is to externally validate the diagnostic performance and clinical usefulness of three ML–based models designed to predict (1) maternal complications, (2) the need for delivery within ≤ 7 days of diagnosis, and (3) the development of HELLP syndrome or placental abruption.

Secondary objectives of this study include:

Improvement of the prediction models by incorporating data from 100 new eoPE cases into the ML training process.Adjustment of the training process to specifically train and optimize the models for the eoPE subgroup with the greatest potential for applicability due to their clinical interest in management: PE diagnosed between 30 + 0 and 33 + 6 weeks of gestation.Conduct a semi-quantitative post-hoc assessment of healthcare professionals’ satisfaction with the information provided by the models to adjust the timing of (1) fetal maturation with corticosteroids, (2) hospitalization, and (3) pregnancy termination.Development of a web application that integrates the data collection and validation process (both quantitative and semi-quantitative) into a single tool accessible to clinicians.

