### Models’ validation strategy

An analysis will be conducted after the inclusion of the first 100 participants to perform an initial external validation of the predictive models. This validation will include both quantitative and semi-quantitative assessments:

The quantitative evaluation will focus on the diagnostic performance of the predicted risks, including the estimation of sensitivity, specificity, positive and negative predictive values, discrimination using the area under the ROC curve, calibration using the Hosmer–Lemeshow test, and clinical utility assessed through decision curve analysis.The semi-quantitative evaluation will consider clinicians’ perceptions of the information provided by the models. After reviewing the model’s information, they will be asked to answer four questions to assess the perceived usefulness and potential clinical impact of the predictions: (1) overall appreciation of the information (“I like it / I don’t like it”); (2) whether this information would have influenced their decision regarding corticosteroid administration (“No / Yes, I would have administered them earlier / Yes, I would have administered them later”); (3) whether it would have modified their management of hospitalization between diagnosis and delivery (“No / Yes, I would have extend the duration of hospitalization / Yes, I would have reduced it”); and (4) whether it would have changed their decision about the timing of delivery (“No / Yes, I would have indicated delivery earlier / Yes, I would have delayed delivery”).

Following this first phase, the ML training methodology will be replicated incorporating the information from the initial 100 cases, and the updated models will then be applied prospectively to the next 100 participants. This “re-training” methodology begins with a preprocessing stage, which includes missing-value imputation using MissForest, outlier removal, standardization of numerical variables with Standard Scaler, and encoding of categorical variables using OneHot and Label encoding [34]. Subsequently, model training is carried out using genetic algorithms within a multi-objective framework. These algorithms are non-deterministic, can be adaptive, and often benefit from parallel computation, enabling them to search for high-quality approximate solutions [35].

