After completing recruitment of 200 patients, a final validation will be performed, formally comparing the discriminative performance of the original and retrained models using the DeLong test for paired ROC curves. Bootstrap resampling will also be considered to derive more robust confidence intervals for key performance metrics, ensuring a stable evaluation of model behavior across samples. In parallel, the semi-quantitative responses from clinicians will be compared between the two phases, providing both an objective and a subjective assessment of model performance and clinical usability.

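### The survey's corticosteroid question asks about the administration decision but offers only timing answers, so withholding, not repeating and 'not applicable' cannot be recorded accurately

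*Protocol article*

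**What the plan says.** Under Models' validation strategy, the protocol article sets out a four-question survey "to assess the perceived usefulness and potential clinical impact of the predictions". Question 2 asks "whether this information would have influenced their decision regarding corticosteroid administration", and its printed answers are "No / Yes, I would have administered them earlier / Yes, I would have administered them later".

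The matching secondary objective, under Objectives, is narrower. It concerns clinicians' satisfaction with the information "to adjust the timing of (1) fetal maturation with corticosteroids", followed by hospitalization and pregnancy termination.

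The Background gives the clinical setting. It notes that "repeated courses appear to be counterproductive, particularly in the long term", and continues: "Current recommendations therefore favor a single course administered within seven days of delivery".

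The answers are then used in a comparison: "the semi-quantitative responses from clinicians will be compared between the two phases", that is, the first 100 participants against the next 100.

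**The concern.** The stem and the answers of question 2 cover different ground. The stem takes in every decision about giving corticosteroids: whether, when and whether again. The answers take in only when. A clinician whose counterfactual decision lies outside timing has to pick an answer that does not describe it.

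Two summaries depend on these answers. One is the proportion of ratings in which the model output would have changed the corticosteroid decision. The other is the direction of that change. A change coded as *No* lowers the proportion. A change coded as *later* keeps the proportion but misstates the direction. A woman for whom timing does not apply, if coded as *No*, cannot be told apart from one whose clinician considered the output and would have changed nothing.

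**Working it through.** No sample-size, power or error-rate formula applies, and the plan states no figure for this item. The check sets the possible decisions against the printed answers.

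| Decision in hindsight | Nearest printed answer | Fit |
|---|---|---|
| Course given; would have given it sooner | *earlier* | exact |
| Course given; would have given it later | *later* | exact |
| No course given; would have given one | *earlier* | loose: no date to move, but it can be read as before delivery and counts as a change |
| Course given; would not have given it | *No* or *later* | none: *No* denies the influence, *later* asserts a course the clinician would not have given |
| Course repeated; would not have repeated it | *No* or *later* | none in general; *later* may fit if the first course is judged to have come too soon |

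Of the five decisions, two fit exactly, one fits loosely and two have no proper answer. No *not applicable* answer is printed either.

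**Can the gap arise?** Nothing in the protocol article says that every participant receives corticosteroids. The Background itself raises repeat courses as a problem, so repetition is not a remote case.

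**Can a clinician skip the question?** The Data handling section says that all form fields are required. It does not say separately whether this includes the survey form. If it does, an inexact answer is forced; if not, some of these ratings may be missing instead.

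**Comparison with question 4.** There the stem asks about the timing of delivery and the answers are earlier or delayed, so stem and answers agree. Question 2 lacks that agreement.

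**Size.** The number of inexact ratings per phase is the share of cases in the last three rows of the table times 100. The share is not in the documents. As an assumption only:

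- 2%: 0.02 × 100 = 2 ratings per phase
- 20%: 0.20 × 100 = 20 ratings per phase

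This range shows scale and is not an estimate.

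**The case against.** The best defence is that the declared objective is timing, and *earlier* or *later* measures exactly that. This stands: the item is not invalid for its stated purpose. It does not remove the mismatch, because the printed stem is wider than both the objective and the answers.

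A second defence is that the Background cites the drawback of repeat courses to explain why timing a single course matters, and gives the models no explicit role in decisions to repeat. This also stands, and it limits how often the gap should matter. It does not give a clinician who would not have repeated a course a way to say so.

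Third, the interface is in Additional file 2, which is not shown, so a comment or not-applicable field cannot be excluded. The article does, however, print the answer list in full.

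Several stronger readings are tempting, but the documents do not support them:

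- *A woman who delivered without a course leaves the clinician with no valid answer.* If the clinician would have given one, *earlier* is workable and records a change.
- *The proportion of change is wrong by a calculable amount.* That needs the share of women without a course, the true rate of change and the assumption that all their changes become *No*. None of these is in the documents.
- *About half the cohort is affected.* The sample-size section assumes that 50% deliver within seven days, so 0.5 × 200 = 100 women would deliver later. For a course given too soon, the existing *later* answer may be the right one. That figure is therefore not a count of misrecorded ratings.
- *The hospitalization question is free of this problem.* Nothing says that every participant is admitted between diagnosis and delivery, so the contrast has no basis.
- *The comparison between phases is biased.* The same item is used in both. A shift would need a different mix of no-course or repeat-course women, and nothing suggests one.

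**Conclusion.** The point holds as a minor measurement issue. Question 2 asks about a decision and offers answers about timing. Withholding, not repeating and *not applicable* cannot be recorded accurately, and giving a course that was not given fits *earlier* only loosely. The reported proportion and direction of change are blurred by an amount that the documents do not allow to be estimated.

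This rests on the stem and answers as printed in the article and on the absence of any statement that all participants receive a course. A reader might conclude that usefulness for the corticosteroid decision is mis-measured as a whole. That goes too far, since the timing objective is covered. The issue touches one of four survey questions in a semi-quantitative assessment; discrimination, calibration and decision-curve analysis do not depend on it.

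**What to change.** Keep the three existing answers unchanged so that the two phases stay comparable. Add one follow-up item with these categories: would have given a course; would not have given it; would have repeated or would not have repeated it; not applicable.

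Where administration data are recorded, report the *earlier*/*later* answers among women who received a course, and report women without a course separately. This split can also be applied to ratings already collected if the record holds those data; the variable list in Additional file 1 is not shown.

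At minimum, limit the stem to timing, in line with the objective, and add a *not applicable* answer.

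The cost is one survey item and one REDCap field, with no new staff. The downside is that recruitment is under way, so ratings made before the change will lack the new item. The date of the change should be recorded so that the two sets can be separated. None of this says which corticosteroid management is right.

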### Web application tool

A dedicated web application has been developed to integrate the ML models into the study workflow and to facilitate both data entry and risk estimation once delivery has occurred. The application was built in Python 3.9 using Flask, a lightweight Python-based web framework that allows efficient and flexible development. The full pipeline adheres to good ML practice principles, including version control of model artefacts, centralized logging of prediction events and critical errors, and full traceability of data exchanges with REDCap™ through structured API calls. For reproducibility and transparency, the full list of Python packages, libraries, and environment dependencies used to implement the web application is provided in Additional file 3.

As represented in Fig. 3, the system is structured in four layers. The user interface (blue box, Table 1) consists of HTML templates which allow clinicians to enter patient data, view model outputs, and complete the post-hoc survey; and static resources which contains a cascading style sheet (styles.css) that control layout and design, improving project organization and scalability.

**Fig. 3 Fig3:**
[figure not shown]
Software architecture of the web-based application tool

**Table 1 Tab1:** Web application HTML templates and associated functionalities

HTML Template	Function
welcome.html	Displays the initial page where the clinician enters the clinical record number. Initiates the workflow that verifies or creates the REDCap™ record
principal_model.html	Main input form for the R model. Allows manual entry or prepopulation of clinical, laboratory, and ultrasound data retrieved from REDCap™
low_risk.html	Informs the clinician that the predicted risk of maternal complications is low (≤ 0.5), indicating that no additional models (HA or T) are required. Provides navigation to the post-prediction survey
submodels.html	Displayed only when the R model predicts a high risk (> 0.5). Collects the additional variables needed to run the HA and T submodels.
submodels_results.html	Presents the prediction results generated by the HA and T submodels. Provides navigation to the post-prediction survey
survey.html	Form allowing clinicians to assess the usefulness of the model outputs after reviewing the predictions
sent_survey.html	Confirmation page indicating that the clinician’s survey responses were successfully recorded in REDCap™. Provides navigation to the welcome page if the clinician wants to introduce a new patient
errors.html	Displays context-specific error messages (invalid API token, inconsistent REDCap™ records or failed data retrieval), guiding the user back to the start of the workflow

All interactions are handled by the Flask application (yellow box, Table 2), which manages routing, session states, data preprocessing, generation of clinical derived variables, prediction requests to the ML models, and communication with the REDCap™ API.

**Table 2 Tab2:** Web Application Routing Structure and associated functionalities

Route	Function
/welcome	Provides navigation to the initial page
/mrn_verification	It is triggered when the clinician enters a MRN in the initial form. Its function is to encrypt the MRN, check whether it already exists in REDCap™, and based on that, either load the corresponding data or create a new record, before redirecting the user to /r_model
/r_model	Shows the main form for the R model, prepopulated with REDCap™ data when available. Validates the API token before loading
/predict_r	Processes all variables for the R model: computes derived parameters, normalizes numeric variables, encodes categorical features, stores key variables in session, runs the R model, obtains the prediction, stores the result in session and determines whether submodels are required
/predict_submodels	Retrieves from the session the variables shared with the R model, processes additional variables for the HA and T models, computes derived parameters, runs both models, obtains the predictions, stores results in session, and redirects to /submodels_results
/submodels_results	Provides navigation to the page that displays the predicted risks for HA model T model. Retrieves record_id from session and sends the models probabilities to REDCap™
/survey	Provides navigation to the page that displays the post-prediction survey. Collects clinician feedback, retrieves record_id from session, sends all information to REDCap™, and confirms successful submission
/next_patient	Clears the session (preserving the API token) and resets the workflow for a new patient

The trained models, their associated scalers, and the categorical-variable mapping file are stored locally on the server as serialized resources (green box) and are loaded by Flask at runtime. The REDCap™ database (red box) acts as the system’s secure data repository. It provides patient information used to prepopulate the web forms and receives the outputs of the prediction models as well as the clinicians’ survey responses. Communication between the web application and REDCap™ is performed through its Application Programming Interface (API), using a site-specific API token that enables authenticated access. All data exchange occurs via POST requests sent to the REDCap™ API endpoint, ensuring secure, structured transfer of clinical information throughout the workflow.

### Workflow

Upon accessing the application, the user enters the patient’s MRN on the welcome page. This identifier is encrypted using a one-way hash function before any query is made. The application connects to the REDCap™ database to check whether the encrypted medical record number exists.

If the encrypted medical record number exists, the corresponding record ID is retrieved and the associated data are automatically loaded into the input forms.If it does not exist, a new REDCap™ record is created with the encrypted identifier, and the forms are displayed empty for manual data entry.

After entering the clinical, analytical, and ultrasound variables, the R model provides the predicted probability of maternal complications.

If the predicted risk exceeds 0.5, the forms for the HA and T submodels are automatically displayed. Once these variables are entered, both predictions are generated, and the clinician proceeds to complete the survey. The model outputs together with the survey responses are then sent to REDCap™.If the predicted risk is lower than 0.5, the clinician is redirected directly to the survey, and the probability estimated by the R model along with the survey responses is stored in REDCap™.

Finally, the application allows the user to reset the session and initiate the workflow for a new patient.

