The development process required addressing the complexity and heterogeneity of the dataset so a structured feature–selection pipeline was implemented using genetic algorithms (GAs), an evolutionary computation technique capable of efficiently searching high-dimensional feature spaces. Two complementary strategies were applied: a mono-objective GA aimed at maximizing the F1-score of each classifier, and a multi-objective GA (NSGA-II) that simultaneously optimized predictive performance and model parsimony, favouring solutions with fewer variables to enhance clinical feasibility [31]. The three models underwent internal validation and demonstrated promising diagnostic performance (sensitivity and specificity of 70%/74%, 69%/88% and 88%/69%, respectively). The R model (K-Nearest Neighbor) included twenty-five predictive variables, the T one (Logistic Regression) included fourteen, whereas the HA (Logistic Regression) incorporated thirteen. Subsequently, simplified versions of the models were derived from the multi-objective strategy: based on only five, seven and three features, achieving a sensitivity of 60%/68%/92% and a specificity of 74%/86%/52% (Fig. 1) [30]. Although the HA model prioritizes sensitivity over specificity, this trade-off may be clinically acceptable, particularly between 30 + 0 and 33 + 6 weeks of gestation, when the maternal risks of continuing the pregnancy increase while neonatal outcomes improve rapidly with gestational age.

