### Sample size estimation

We will evaluate 5 candidate predictors for the R model, 7 for the T model, and 3 for the HA model as specified in Fig. 1. Following the recommendation of having at least 10 events per predictive variable and assuming that:

Approximately 50% of women with eoPE deliver within ≤ 7 days [14], the required sample size to validate the T model is: 7 (predictive features) x 10 (events) / 0,5 (event incidence) = 140 eoPE casesApproximately 40% of women with eoPE experience any PE-related complication, and in 20% these complications include placental abruption or HELLP syndrome [30]. According to this, the required sample size to validate the R model is: 5 (predictive features) x 10 (events) / 0,4 (event incidence) = 125 eoPE cases, and to validate the HA model is: 3 (predictive features) x 10 (events) / 0,2 (event incidence) = 150 eoPE cases

This estimation assumes independence among predictor variables. However, ML techniques can identify dependencies between variables when present, which could potentially reduce the required sample size. Nonetheless, we have chosen to maintain the estimate of 200 cases, as it is the most conservative assumption and aligns with the sample size used in our previous work during model development, providing greater confidence.

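### The application scores T and HA only when R exceeds 0.5, but the objective and sample size treat all enrolled women as scored; T very probably falls short of its own event target and HA probably does

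*Protocol article*

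**What the plan says.** The Abstract states that the study's predictions are produced by the web application after delivery. The Workflow section describes a sequence: R is run first, and "If the predicted risk exceeds 0.5, the forms for the HA and T submodels are automatically displayed". For the other branch the text is: "If the predicted risk is lower than 0.5, the clinician is redirected directly to the survey". In that branch REDCap receives only the R result and the survey answers. Table 1 repeats the gate. The submodel page is "Displayed only when the R model predicts a high risk (> 0.5). Collects the additional variables needed to run the HA and T submodels", and the low-risk page carries the message "indicating that no additional models (HA or T) are required". No other scoring route is described.

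The Background presents T and HA as second-stage models for women classed as high risk by R. The Objectives section, however, makes external validation of all three models the primary objective, with no restriction of T or HA to that group. The Sample size estimation section applies ten events per predictor to incidences among all women with early-onset preeclampsia. For HA it reads "3 (predictive features) x 10 (events) / 0,2 (event incidence) = 150 eoPE cases"; the same formula gives 140 for T and 125 for R, and the total is set at 200. The Models' validation strategy section lists the performance measures but names no analysis set for T or HA.

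**The concern.** Followed as written, the application yields no T or HA prediction for a woman with R at or below 0.5. Sensitivity, specificity, predictive values, AUC, calibration and decision curves for T and HA, if taken from the stored predictions, would then be conditional on a positive R result. The sample size calculation makes no allowance for this.

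Two things are at stake. The first is the number of events behind two of the three models in the primary objective. The second is how events below the gate are counted:

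- HELLP or abruption in an R-low woman counts as a miss of R, because both are components of the R outcome, but not as a miss of HA.
- Delivery within 7 days in an R-low woman without a complication counts against no model.

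The planned paired DeLong comparison is also exposed. It needs original and retrained predictions for the same women, and a retrained R may pass different women through the gate.

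**Working it through.** **Inputs from the protocol article.**
- Sample size estimation: incidence 40% for any complication, 20% for HELLP or abruption (applied to all cases in the formula) and 50% for delivery within 7 days; ten events per predictor; 5, 7 and 3 predictors for R, T and HA; total 200.
- Background: R sensitivity and specificity of 60% and 74% (simplified), or 70% and 74% (full). The predictor counts in the sample size section are those of the simplified models.

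**Step 1: the plan's own figures.** N = predictors × 10 / incidence.
- T: 7 × 10 / 0.5 = 140
- R: 5 × 10 / 0.4 = 125
- HA: 3 × 10 / 0.2 = 150

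All three reproduce. The implied targets are 70 events for T and 30 for HA. With all 200 women scored, one expects 200 × 0.5 = 100 T events and 200 × 0.2 = 40 HA events, so both targets are met.

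**Step 2: share of women passing the gate.** P(R > 0.5) = incidence × sensitivity + (1 − incidence) × (1 − specificity).
- Simplified R: 0.40 × 0.60 + 0.60 × 0.26 = 0.396, or 79 of 200
- Full R: 0.40 × 0.70 + 0.60 × 0.26 = 0.436, or 87 of 200

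This share is not stated in the protocol. As an illustration of its range, R at 50%/90% would give 0.26 and R at 70%/60% would give 0.52.

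**Step 3: T events above the gate (simplified R).** The early-delivery rate among R-high women is not given, so it is varied. Events = 79.2 × rate; women to recruit for 70 events = 70 / (0.396 × rate).

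| Assumed rate | T events of 200 women | Women needed for 70 events |
|---|---|---|
| 50% | 40 | 354 |
| 60% | 48 | 295 |
| 70% | 55 | 253 |
| 80% | 63 | 221 |

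The break-even rate is 70 / 79.2 = 88%. With the full R model it is 70 / 87.2 = 80%. If early delivery were independent of R, about 60 of the 100 early deliveries would lie below the gate.

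**Step 4: HA events above the gate (simplified R).** If R detects HELLP or abruption at its overall 60%, 40 × 0.60 = 24 events pass and 16 do not. The full R model gives 40 × 0.70 = 28. Reaching 30 needs R to detect 30 / 40 = 75% of these events.

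The 60% is an assumption. Of 200 women, 80 have a complication; R detects 48 and misses 32. Since 40 of the 80 are HA events, at least 40 − 32 = 8 and at most 40 pass the gate. R's sensitivity for HELLP or abruption can therefore lie anywhere from 20% to 100%, and the women needed for 30 events from 30 / (0.2 × 1.0) = 150 to 30 / (0.2 × 0.2) = 750, with 250 at 60%.

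**Step 5: the first validation, at 100 women.** About 40 women would be scored, with about 20 T events (at a 50% rate) and about 12 HA events (range 4 to 20).

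**Step 6: precision.** The approximate 95% half-width for a sensitivity is 1.96 × √(p(1 − p)/n).
- T at 0.68: 0.09 with 100 events, 0.15 with 40
- HA at 0.92: 0.08 with 40 events, 0.11 with 24, 0.15 with 12

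**The case against.** Four counter-arguments deserve weight.

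**The gate is the intended use.** The Background places T and HA after a positive R, and evaluating a second-stage test in the women who would receive it is legitimate. This stands. It does not remove the conflict, because the objective is unrestricted and the sample size rests on the whole cohort.

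**Offline scoring is not excluded.** All model variables are recorded for every participant, the validation section never limits the analysis to values stored by the application, and the paired DeLong test suggests that some scoring outside the clinician's workflow will be needed. An analysis plan may settle this. That too stands, and it means nothing is irrecoverably lost. But the only route described is the application, and the two sections disagree as published.

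**Missed cases are not simply uncounted.** A reader might infer that HELLP or abruption below the gate disappears from the evaluation, or that the sensitivity of the two-step pathway cannot be estimated. The documents support neither. Such cases are R false negatives. The R probability is stored for R-low women and their outcomes are collected, so cascade sensitivity for HA can be calculated by treating R-low women as test-negative. The article simply does not name that measure.

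**The HA figures rest on one assumption.** It is tempting to say that the cascade detects 0.60 × 0.92 = 55% of HELLP or abruption and not 92%, or that HA certainly misses its target. Both need R's sensitivity for these two events to be fixed at 60%, and the plan's figures allow 20% to 100%. The article also does not say whether the 92% was obtained in all women or in R-high women.

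**Conclusion.** The concern holds as an inconsistency between the scoring workflow, the primary objective and the sample size basis. Followed as written, the design does not deliver the event counts it sets itself.

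The firmer shortfall is for T: about 40 to 63 events at early-delivery rates of 50% to 80%, against 70, with about 88% needed to break even. For HA, about 24 events against 30 is the central estimate and a shortfall is likely, but the range of 8 to 40 includes the target.

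These figures assume that R performs externally as in development (simplified version), that 40% of women have a complication, and that no scoring takes place outside the application. T and HA results from the stored predictions describe R-high women only and should not be presented as whole-cohort performance.

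**What to change.** - Score R, T and HA for all participants in a batch run from REDCap, with both the original and the retrained versions. Keep the R > 0.5 gate only for what the clinician sees. Retrained scores in the first 100 women are training-set scores and should not be read as validation.
- Report T and HA in all women, in R-high women, and as the full cascade with R-low women counted as test-negative.
- If only R-high women are to be analysed, state this in the Objectives and the Models' validation strategy sections, and restate the event counts in Sample size estimation for that subset, with the assumed gate share and early-delivery rate shown.
- While recruitment continues, check that the T and HA predictors are complete in REDCap for R-low women. The application asks for them only above the gate, and it allows records to be created by manual entry.

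The cost is a scoring script, a paragraph of analysis wording and a completeness check. No new variables are needed, the clinician's display does not change, and participants are not affected.
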